### Management of AEs

- Free medical care is provided for AEs related to the procedure, including surgical care if needed. If referral for medical or surgical complications is required, participants are referred to the Kalisizo Hospital (2-3 minutes driving time), the Rakai Hospital or hospitals in the neighboring District of Masaka (approximately 30 minutes driving time).

### Reporting of AEs

- All AEs are ascertained and documented by Program medical officers

- All deaths and SAEs are notified to the Ugandan and U.S. PIs within 48 hours, by e-mail or fax.

- The U.S. and Ugandan PIs then notifies the relevant IRBs (Johns Hopkins, Columbia University and Uganda Virus research Institute) in writing as soon as possible, and not later than 10 days after identification of the SAE. The nature, severity, timing and relationship of the AE to circumcision or study medications is specified by the medical officer. A summary of how the severity and relationship to study participation was determined is provided by the PI, and clarifications are made by phone with the medical officer as needed.

.

### Tabulations of AEs

- The PI will submit aggregate reports of all AEs and tabulations via the Program Statisitician to the DSMB. AEs will be described by type, time since surgery or medications, severity and relationship to study treatments. Dates of AEs are also tabulated to assess temporal trends or patterns.

- AEs are tabulated by total number, and by number of AEs per individual for those participants experiencing more than one AE**.**

### Source documentation

**-** Operative and postoperative AEs use Rakai Health Sciences Program documentation (Forms 11)

- Medical visits to health centers or other facilities outside of the Rakai Health Sciences Program cannot be completely documented due to poor records. We endeavor to obtain copies of hospital medical records where feasible, after obtaining permission from the index person. Rakai Health Sciences Program reports (such as questionnaires), are used to provide information.

- To maximize documentation Rakai Health Sciences Program offers free medical care or referral for injury or illnesses as a result of study participation. Phone numbers of medical officers are provided on the Postoperative patient Information Sheet (Form 46), we provide transport if needed and reimburse participants for transport costs. In addition, we arrange community health workers to provide a contact person in each village who can facilitate contact with the Project. Recordsare maintained for unscheduled visits (Form 16), and an AE report completed if indicated**.**

# STATISTICAL CONSIDERATIONS

## Preamble

There are several trial end points including:

- circumcision safety

- circumcision acceptability

- circumcision efficacy for prevention of HIV acquisition in HIV-negative men

- circumcision efficacy for prevention of STD acquisition in HIV-negative and HIV-positive men

- circumcision efficacy for prevention of male-to-female HIV and STD infections

- the effects of circumcision on behavioral disinhibition.

As noted previously this Gates supported study is an individually randomized, unblinded trial of male circumcision in ~ 800 HIV-positive men and~ 1000 HIV-negative men who decline VCT, to be conducted in conjunction with a NIH supported trial of 5000 HIV-negative men who accept VCT. The sample size estimates for safety and acceptability of circumcision are based on the number of men enrolled in the Gates trial. The sample size for the end point of HIV acquisition in circumcised and uncircumcised HIV-negative men is based on the combined Gates (n ~ 1000) and NIH (n ~ 5000) populations. The NIH trial is independently powered for an HIV incident end point and the 1000 HIV- men contributed by the Gates trial component enhance this power and allow analyses of subgroups. However, the 1000 men enrolled in the Gates trial will not provide power for an independent HIV end point.

The end points of HIV transmission from HIV-positive men to HIV uninfected women in relationships with circumcised and uncircumcised men, are based on the population of HIV+ men enrolled in the Gates trial, and anticipated HIV seroconverters from both the NIH and Gates trials.

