## Rationale

Observational data and three randomized trials show that male circumcision reduces the rate of HIV infection in men by approximately 50-60%. Thus circumcision is an important public health measure because, despite initial costs, it could provide long-term risk reduction in males and secondary protection against infection in their female partners, without incurring recurrent costs. However, the possible efficacy of circumcision for prevention of HIV in women is unclear.

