***a. NIH Supported trial of male circumcision for prevention of HIV and STD acquisition in HIV- men.***

NIH has supported a trial of 5,000 HIV-negative men who agree to learn their HIV results. The trial was closed early due to efficacy on December 12, 2006, and a paper reporting the findings has been published in Lancet. Circumcision is now being offered to all HIV-negative controls.

***b. Gates Foundation supported trial male circumcision: STD, HIV and behavioral effects in men, women and the community.***

The complementary but separate Gates Foundation supported trial enrolled HIV+ men and men who decline to learn their HIV results. This trial has been conducted concurrently in the same communities as the NIH funded trial, using identical procedures.

In addition, the Gates sponsored study is assessing the safety of circumcision in HIV+ men, the efficacy of circumcision to prevent HIV and STDs in female partners, and the effects of circumcision on risk behaviors (i.e., disinhibition) in enrolled men, their partners and the community.

This protocol summarizes the Gates Foundation trial.

#

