## Female HIV Acquisition*.*

Information on women will be derived from the RCSS surveillance surveys, and women are not enrolled in the male circumcision trials. Female HIV acquisition associated with the male partner’s circumcision status will be assessed among HIV-negative women in relationships with HIV-positive men. Please note, we do not enroll HIV-discordant couples; the men are individually enrolled in the circumcision trials and the women individually enrolled in the RCSS. Couples linkage will only be done retrospectively after completion of the trials, although promotion of couples VCT will be ongoing throughout the study. The information on male partner circumcision and HIV status will be derived from this retrospective linkage.

Our observational data in HIV-discordant couples found a male-to-female transmission incidence of 5.2/100 py if the male was circumcised and 13.2/100py if the male was uncircumcised (RR = 0.39). (Please note, we strongly promote condoms and couples counseling, but acceptance of these services within married couples is low). We estimate sample sizes required to detect an efficacy of this magnitude, with  = 0.05 and 1- = 0.80. The person years accrued for female exposure in discordant couples with an HIV+ male partner can be estimated from the number of prevalent and incident discordant couples with HIV+ men, as follows:

***i.*** *Person years contributed by prevalent HIV+positive men in discordant relationships with HIV- negative women:* We estimate that 500 HIV positive males per arm will accept enrollment . From prior data, 80% of men can be linked to a female partner and 55% of prevalent HIVpositive men have HIV-negative female partners. Thus we expect 220 HIV prevalent males in a discordant relationship (i.e., 500 x 0.8 x 0.55). Assuming

85% annual follow up, we estimate that 220 HIV-discordant, male HIV+/female HIV- couples, will provide 186 py in the 1st follow up year and 158 py in the 2nd follow up year, yielding a total of 344 person years in exposed, initially HIV- women. With 344 py per arm, will have 85% power to detect a RR = 0.39. Assuming 7.5% contamination, the sample size is sufficient to detect a RR* of 0.41 with 80% power.

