### Female HIV Acquisition

We propose an intent-to-treat analysis . The unit of analysis is women in relationships with HIV-positive male partners. Although the male’s circumcision status can be ascertained by interview with the female partner, the male’s HIV status can only be determined by linking couples from within the RCSS. This will be done at the conclusion of follow up. The linkage will allow identification of men enrolled in the circumcision trials, determine their randomization arm and their HIV status, and provide an objective measure of circumcision status as well as the timing of the circumcision.

We will determine male-to-female transmission (female HIV incidence per 100 py) in the circumcision arm relative to control using multivariate Poisson regression as described for male HIV acquisition in 8.9.a above.

Data are also collected on the frequency of intercourse, so in addition, we will estimate the probability of HIV infection per coital act among circumcised and non-circumcised men using published methods.20,116 The probability of transmission in the ith couple (Pi) can be written as 1- (1-) n i, where ni is the number of acts during the follow up period, and the infectivity () is the probability of transmission per act.116 Allowing the infectivity to depend on covariates through a complementary log-log link, leads to the regression model [log -log (1-P)] = log ni + b0 + b1X1 where b1 and X1 are vectors of regression coefficients andcovariates, respectively. This model will be fit using statistical methods for generalized linear models, specifically binomial regression with a complementary log-log link and offset term log ni (SAS Institute Inc., Cary, NC.). The comparisons will again be between circumcision arm and control. We have shown that the probability of male-to-female HIV transmission per coital act is 0.0004 if the malepartner was circumcised and 0.0015 if the male was uncircumcised (RR = 0.27, unpublished).

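### The intent-to-treat comparison of female HIV acquisition takes in partners of men who seroconvert after randomization, a subset that the intervention itself shapes

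*Protocol*

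**What the plan says.** Three places in the protocol define who enters the female HIV acquisition comparison.

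- Section 8.1 (Preamble) says that the male-to-female transmission end points "are based on the population of HIV+ men enrolled in the Gates trial, and anticipated HIV seroconverters from both the NIH and Gates trials".
- Section 8.4 (Female HIV Acquisition) says that the exposed women's person-years "can be estimated from the number of prevalent and incident discordant couples with HIV+ men". The calculation that follows covers only men who are HIV-positive at enrolment.
- Section 8.8.2 (Female HIV Acquisition) opens with "We propose an intent-to-treat analysis" and adds: "The unit of analysis is women in relationships with HIV-positive male partners". The man's status is established by linkage when follow-up ends: "The linkage will allow identification of men enrolled in the circumcision trials, determine their randomization arm and their HIV status". The arms are then compared by Poisson regression. The analysis plan does not separate men HIV-positive at enrolment from men infected later. The only stratum named in advance is the man's viral load.

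Two further statements matter. Section 1.3 describes the NIH population: "NIH has supported a trial of 5,000 HIV-negative men who agree to learn their HIV results". An NIH couple can therefore enter this comparison only if the man seroconverts during the trial. Section 1.2 states that "male circumcision reduces the rate of HIV infection in men by approximately 50-60" per cent, and section 8.2 plans on a male rate ratio of 0.53.

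**The concern.** An intent-to-treat comparison keeps the benefit of randomization only if membership of the analysis set is fixed before treatment can act. For partners of men HIV-positive at enrolment it is. For partners of seroconverters it is not: the man qualifies through an event that circumcision is expected to roughly halve. The number of these couples differs by arm by design, and the men who make up the subset need not be comparable between arms.

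If partner incidence in these couples is not the same as in prevalent couples, the unequal mix moves the pooled rate ratio even when circumcision has no effect on male-to-female transmission. Part of the effect on male acquisition would then show up in the estimate for women. Section 2.1 makes efficacy in women and safety for partners of HIV-positive men primary objectives, so the population behind this estimate should be one that randomization protects.

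**Working it through.** **1. The plan's own person-years (section 8.4).** 500 HIV-positive men per arm × 0.80 linked × 0.55 discordant = 220 couples. With 85% annual follow-up, 220 × 0.85 + 220 × 0.85² = 187 + 159 = 346 person-years (py) per arm. The protocol has 344, so this reproduces apart from rounding. It contains no seroconverter person-time. Each prevalent couple supplies 344/220 = 1.56 py.

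**2. Power at 344 py.** With 13.2 and 5.2 per 100 py, the expected events are 45.4 and 17.9. On the log rate ratio, 0.932/√(1/45.4 + 1/17.9) = 0.932/0.279 = 3.34, which gives 92% power two-sided at 0.05. Other standard methods give up to 96%. The stated 85% is not reproduced, but the difference is on the safe side and does not affect this point.

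**3. Expected seroconverters per arm.** Control = py × 0.018; intervention = control × 0.53. Couples = seroconverters × 0.80 × 0.55. The 0.55 is given only for prevalent men, so its use here is an assumption.

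| Male py per arm | Control men | Intervention men | Control couples | Intervention couples |
|---|---|---|---|---|
| 3,932 (NIH alone) | 70.8 | 37.5 | 31 | 17 |
| 5,188 (both trials, section 8.2) | 93.4 | 49.5 | 41 | 22 |

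The ratio is 1/0.53 = 1.9 to 1 in either row. The 1,256 py that section 8.2 adds for the Gates men looks like a two-arm total, since 400 × (0.85 + 0.85²) = 629. With 3,932 + 629 = 4,561 py the couples are 36 and 19, between the two rows.

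**4. Shift of a true null.** A woman in an incident couple is exposed only after the man seroconverts, so the couple supplies less than 1.56 py. Take 0.75 py (assumption). Let k be partner incidence in incident couples relative to prevalent couples, the same in both arms (assumption; not in the protocol). With C and I the incident-couple py in the control and intervention arms:

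RR = [(344 + kI)/(344 + I)] / [(344 + kC)/(344 + C)]

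- NIH alone: C = 31 × 0.75 = 23.25, I = 17 × 0.75 = 12.75.
  - k = 2: (369.5/356.75)/(390.5/367.25) = 1.036/1.063 = 0.97
  - k = 3: (382.25/356.75)/(413.75/367.25) = 1.071/1.127 = 0.95
- Both trials: C = 41 × 0.75 = 30.75, I = 22 × 0.75 = 16.5.
  - k = 2: (377/360.5)/(405.5/374.75) = 1.046/1.082 = 0.97
  - k = 3: (393.5/360.5)/(436.25/374.75) = 1.092/1.164 = 0.94
  - k = 0.5: (352.25/360.5)/(359.375/374.75) = 0.977/0.959 = 1.02
- k = 1 gives exactly 1.00 in every case.

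**5. Range.** Letting time at risk run from 0.5 to 1.0 py and discordance from 55% to 90%, incident couples supply about 4-16% of control and 2-9% of intervention female person-time. At k = 3 the null then moves to between 0.90 and 0.95.

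**6. Against sampling error.** Under the null there are about 344 × 0.132 = 45 events per arm, so the standard error of the log rate ratio is √(2/45.4) = 0.21. The shifts in step 4 for k = 2 and 3 are 0.03 to 0.06 on the log scale, about 0.1 to 0.3 of a standard error.

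**The case against.** The best counter-argument is that pooling is inferred. Section 8.1 speaks of what the end points are based on. Section 8.4 announces incident couples but assigns them no person-time, and section 8.8.2 names neither seroconverters nor the NIH trial. An SAP could keep the two groups apart. That holds as far as it goes, but two sections include these couples in terms, and the third gives a unit of analysis and a linkage rule that admit them. As the protocol stands they are in.

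It is also fair that unequal numbers alone do not bias a rate ratio. At k = 1 there is no bias, and nothing in the protocol says how k departs from 1. The NIH trial has closed early and its controls are being offered surgery (sections 1.3 and 6.1b), so the planned person-years and the contrast in seroconversion may not be reached. These points limit the size of the bias. They do not make the subset randomized.

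Three stronger readings that a reader might infer are not supported:

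- *That pooling hides the harm signal.* The signal in sections 1.1 and 10.7.3 was largely among couples who resumed sex before wound healing. It is followed up by weekly wound checks of all HIV-positive men, an added 18-month visit for them and their partners, and DSMB review. A shift of at most about 0.3 of a standard error at k up to 3 does not show masking.
- *That circumcised men who seroconvert are more highly exposed.* They may differ in exposure, but no passage says so or gives a figure.
- *That the whole comparison loses its randomized basis.* Roughly 84-98% of person-time, depending on arm and assumptions, comes from men HIV-positive at enrolment, where randomization holds.

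**Conclusion.** The point holds in a limited form. As written, the comparison labelled intent-to-treat combines a randomized population with a smaller one selected on a post-randomization event that the intervention changes. About twice as many such couples are expected among controls: 41 against 22 for both trials, or 31 against 17 for NIH alone.

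The mechanism follows from the protocol's own statements. The size does not, because it rests on an assumed multiplier, 0.75 py per incident couple, and discordance carried over from prevalent men. Under those assumptions a true null of 1.00 becomes about 0.97 at a multiplier of 2 and 0.94-0.95 at 3. It stays at 1.00 when the multiplier is 1 and moves the other way below 1. The bias is modest, but the change that avoids it is inexpensive and should be made.

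**What to change.** In sections 8.1, 8.4 and 8.8.2, define the primary female HIV acquisition population as initially HIV-negative women linked to men who were HIV-positive at enrolment, analysed by the man's assigned arm. Report partners of men who seroconvert after enrolment separately, as a descriptive analysis that randomization does not protect.

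The man's HIV status at enrolment is already known from screening, so no new data are needed. The definition should not require that the couple be partnered on the date of randomization. Women are seen at annual cohort surveys, linked retrospectively, or invited through walk-in men (sections 8.4, 9.3 and 9.4), and that date may not be recoverable.

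The cost is the extra incident-couple person-time, about 31 py in the control arm and 17 py in the intervention arm under the assumptions above (both trials). None of it is in the power statement, and the 344 py per arm behind that statement are kept in full.

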### Initial Assessment of Safety.

We initially assessed of safety after completing the first 100 circumcision patients who received intensive postoperative follow up . This was followed by a pause in enrollment to evaluate safety.

The frequency of complications following adult circumcision in the Rakai trials is approximately 3.6%. However, review of the surgical literature suggests that complications occur in approximately 2% of patients, and what we define as moderate or severe AEs occur in approximately <0.5% of surgeries. The literature is based on clinical case reports, and the intensity of ascertainment or duration of observation cannot be fully assessed. It is possible that the intense surveillance and careful definition and probing for complications in this research study may differ from these case series, and that our estimates of frequency of events, especially minor AEs which are more likely to detected by intensive surveillance may be incorrect (i.e., we may observe a higher frequency than that reported in the surgical literature as a result of more intensive ascertainment and definitions of minor events**).**

Our initial assessment of safety was based on the first 100 circumcisions performed. Assuming that the expected number of AEs were < 2%, and that moderate and severe AEs were < 0.5% (based on limited data from surgical case series), we used StatXact to construct exact 95% confidence intervals and exact one-sided p-values for a **binomial proportion with N =** 100, to compare the number of observed AEs against two “null” hypotheses; a) that all AEs will be < 2.0% and b) that moderate/severe AEs will be < 0.5%. These estimates are shown in Table 4.

There were less than six AEs observed in Stage 1, the 95%CI still contained 2%, compatible with the anticipated rate, and the study proceeded as planned. (Note: the DSMBs reviewed AEs in Stage 1 and agreed that the trials could proceed.)

As noted above, intensive postoperative surveillance might yield higher rates of minor AEs, relative to those reported in routine case series. Therefore, it is necessary to carefully consider the severity of AEs observed, before making a judgement on whether observed AEs exceed the expected numbers.

### Ongoing Monitoring of Circumcision Safety During the Trials

Please note, these estimates are based on the total populations of HIV- men enrolled in the Gates and NIH trials

Surgical and postoperative complications were expected to be ~2%, and were monitored continuously during stage one and periodically in Stage 2 (at approximately 4-7 months, ~20 and ~40 months) to ensure safety. Monitoring of the rate of complications associated with circumcision is done using similar techniques described for monitoring efficacy. To facilitate the proper analysis of this continuous safety data, we propose to use the methods of Lan, Rosenberger, and Lachin in which they demonstrate how to construct a sequential boundary (Wald boundary) for a Z‑statistic used to continuously monitoring data that maintains an overall Type I error rate. The methods build upon the spending‑function methods of Lan & DeMets, and can also be used when switching from occasional (e.g. group sequential) monitoring to continuous monitoring.

We planned to conduct interim analyses if required for DSMB safety assessment at 20 and 32 months. We expected to have completed 1,500 circumcisions by 20 months and 3,000 by 32 months. Using StatXact (Cytel Software Corp), we estimated the smallest number of AEs that would give an exact 1-sided 95% lower confidence bound on the estimated rates of AEs (not adjusted for interim analyses). With 1,250 men circumcised by 20 months, if the total AE rate  2.64% (33 events), the lower 95% CI bound would significantly exceed the expected rate of 2.0% (25 events), and for moderate/serious AEs, a lower 95% CI bound of an observed rate of 0.88% (11 events) would significantly exceed the expected rate of 0.5% (7 events). Similarly, at 32 months with 2,500 surgeries completed, if the total AE rate  2.48% (62 events), the lower 95% CI would exceed the expected 2.0% rate (50 events), and for moderate/serious AEs, with an observed rate of 0.72% (20 events), the lower 95% CI would exceed the expected rate of 0.5% (13 events)

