## Interim Data and Safety Monitoring

It was suggested that DSMB review accrual of data at ~ 20 months (accrual of 2870 subjects), 31 months at which time all subjects will have been enrolled, and two year data would be available for the first 200 participants, and at month 40 when 2-year follow up data would be available on 80% of volunteers.

The DSMB monitored the ethical conduct of the study and evaluated accumulating data for adverse and beneficial treatment effects. We requested Ugandan representation to address specific cultural, religious and other issues. [name], Director of the Program on Bioethics at UCSF, and member of the National Bioethics Advisory Commission (NBAC), assists us with ethical issues. At the first meeting, the design and methods for conducting the pilot study was reviewed, and criteria developed for evaluating the pilot study to determine whether to initiate the clinical trial. We also proposed that the DSMB considers the following criteria for continuation of the randomized trial:

***Safety.*** The expected rate of total AEs following circumcision was expected to be ~ 2%. This was continuously monitored during the trial and specifically assessed by the DSMB after the first 100 surgeries, and at 20 and 31 and 40 months.

***Acceptability.*** Acceptability of circumcision should be about 50% among eligible men. If acceptance is less, the DSMB will evaluate the data from the pilot study to determine whether to proceed with the full-scale randomized clinical trial, to change accrual methods or to propose an alternative design.

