We firmly believe that exclusion of HIV positive men from these trials would create major ethical dilemmas and preclude the investigation of important safety issues critical to future programmatic and clinical practice. Thus, we believe that these trials can only be ethically conducted in a community setting if both HIV-negative and HIV-positive men are enrolled*.* We anticipate that the DSMB would carefully scrutinize data on circumcision of HIV positive men, and if the DSMB found evidence of risk to either to HIV positive men or their partners, the study would modified according to DSMB recommendations **The findings at the December 19, 2006 and March 1, 2007 reviews suggested non-significant higher rates of male-tofemale HIV transmission in the intervention arm, largely among couples who resumed sex prior to wound healing. The moderate and severe surgical complications among HIV+ men (3.2%) were comparable to those in HIV-negative men (3.6%), although wound healing may have been somewhat slower in the HIV+ men. Circumcision reduced the rates of GUD in HIV+ men.**

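### Three of the four adverse-event thresholds in section 8.1.2 miss their own exact criterion by one event, the fourth prints the wrong rate, the denominators conflict, and the 0.5% boundary no longer discriminates at the reported rates

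*Protocol*

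**What the plan says.** Section 8.1.2 of the protocol describes its method this way: "we estimated the smallest number of AEs that would give an exact 1-sided 95% lower confidence bound on the estimated rates of AEs". It adds that the counts are "not adjusted for interim analyses". The reference rates are 2.0% for all adverse events and 0.5% for moderate/serious events. Section 8.1.1 takes both from surgical case series and warns that closer surveillance in this study may find more.

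The section gives four thresholds:
- 33 (2.64%) and 11 (0.88%) at 1,250 surgeries
- 62 (2.48%) for all events at 2,500 surgeries
- for the more serious events at 2,500 surgeries: "for moderate/serious AEs, with an observed rate of 0.72% (20 events), the lower 95% CI would exceed the expected rate of 0.5% (13 events"

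Just before these, the section says "We expected to have completed 1,500 circumcisions by 20 months and 3,000 by 32 months".

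On the population, section 8.1.2 says "these estimates are based on the total populations of HIV- men enrolled in the Gates and NIH trials". The preamble in section 8.1 says "The sample size estimates for safety and acceptability of circumcision are based on the number of men enrolled in the Gates trial".

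On rates, section 8.9 still carries the earlier expectation: "The expected rate of total AEs following circumcision was expected to be ~ 2" per cent. Section 10.7.3 reports observed figures: "The moderate and severe surgical complications among HIV+ men (3.2%) were comparable to those in HIV-negative men (3.6" per cent). Section 8.1.1 gives a complication frequency of about 3.6% in the Rakai trials without saying which severities it covers.

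**The concern.** The four counts are stated decision thresholds for the DSMB, and the criterion behind them is exact, so each count either meets it or does not. If a count is one too low, the protocol claims a statistically significant excess that its own rule does not support. If a rate and a count disagree, the reader cannot tell which one governs.

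Two further points affect whether the thresholds are of use. A boundary set at 0.5% tells the DSMB nothing when the accepted rate in the same document is above 3%. And primary objective 2 is safety in HIV-positive men and their partners, while the thresholds are derived for HIV-negative men.

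**Working it through.** **Inputs.** Null rates p0 of 2.0% and 0.5%, the counts, and n of 1,250 and 2,500 or 1,500 and 3,000 come from section 8.1.2. The observed rates of 3.2% and 3.6% come from section 10.7.3, and the 3.6% of unstated severity from section 8.1.1.

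**Formula.** The exact one-sided 95% lower bound for x events in n is the 5th percentile of a Beta(x, n − x + 1) distribution. It exceeds p0 exactly when P(X ≥ x | n, p0) < 0.05.

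**The plan's own counts.**

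| Printed threshold | x/n | Null | Lower bound | P(X ≥ x) | Meets rule? | Smallest count that does |
|---|---|---|---|---|---|---|
| 33 of 1,250 | 2.64% | 2.0% | 1.94% | 0.069 | no | 34 (2.72%; bound 2.007%, P = 0.048) |
| 11 of 1,250 | 0.88% | 0.5% | 0.494% | 0.053 | no | 12 (0.96%; bound 0.555%, P = 0.026) |
| 62 of 2,500 | 2.48% | 2.0% | 1.990% | 0.054 | no | 63 (2.52%; bound 2.026%, P = 0.041) |
| 20 of 2,500 | 0.80% | 0.5% | 0.531% | 0.030 | yes | 20 |
| 0.72% of 2,500 = 18 | 0.72% | 0.5% | 0.466% | 0.084 | no | 20 |

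The last two rows are one printed item. Its count is right, since 19 events give a bound of 0.498% and P = 0.051. Its rate is wrong: 20/2,500 = 0.80%, and 0.0072 × 2,500 = 18.

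**Could another method explain the counts?** The smallest counts, in the order of the four printed thresholds (33, 11, 62, 20), are:
- strict tail P(X > x) < 0.05: 33, 11, 62, 19
- mid-p: 34, 11, 62, 19
- Wilson: 34, 11, 62, 19
- Wald: 35, 12, 63, 20
- Poisson: 34, 12, 63, 20

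None gives all four printed counts.

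**With the surgeries the section expects.** The smallest counts are:
- n = 1,500: 40 (bound 2.019%, P = 0.045) and 13 (bound 0.513%, P = 0.042)
- n = 3,000: 74 (bound 2.019%, P = 0.043) and 23 (bound 0.525%, P = 0.032)

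For all events this moves the thresholds from 33 to 40 and from 62 to 74, far more than the one-event errors.

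**The 0.5% boundary at the reported rates.** 3.2/0.5 = 6.4 and 3.6/0.5 = 7.2.
- In 1,250 surgeries the expected number of moderate/severe events is 1,250 × 0.032 = 40 to 1,250 × 0.036 = 45, against a threshold of 11. The probability of staying below 11 is about 1 × 10⁻⁸ at 3.2% and smaller at 3.6%. With 12 as the threshold it is about 4 × 10⁻⁸ at 3.2%.
- In 2,500 surgeries, 80 to 90 events are expected against a threshold of 20.

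**The 2% boundary.** The only other observed figure is the 3.6% of unstated severity in section 8.1.1, and 3.6/2.0 = 1.8. At 3.6% the probability of reaching 33 in 1,250 is 0.976 and of reaching 62 in 2,500 is 0.999. The document gives no total adverse-event rate defined in the same way as the 2% null.

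**Population, side by side.** Section 8.1: safety rests on men in the Gates trial, who include the HIV-positive men. Section 8.1.2: the estimates are for HIV-negative men from both trials. The two disagree, and no section gives a count or rate for HIV-positive men.

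**The case against.** The strongest reply is that the one-event errors change no decision. With 40 to 45 events expected against 11 or 12, the boundary is crossed either way. That is true of the moderate/serious line at the reported rates. It does not excuse a threshold that fails its own definition, and the conflict in denominators is larger.

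Second, the comparison sign before 2.64% and 2.48% did not survive in the text available for this review. If it was a strict greater-than sign, the two all-event thresholds would be right. The wording asks for the smallest qualifying number, however, and the 11-event item has no missing sign.

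Third, the section is largely in the past tense, concerns looks that were planned only if required, and set its nulls in advance from case series. Exceeding a preset null is what a safety rule should flag. This stands. Crossing the boundary is not a defect in the rule. The fault is that section 8.9 keeps the 2% expectation and nothing says the 0.5% boundary has been passed.

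A reader might also infer stronger points that the documents do not support:
- **That every threshold fails.** The count of 20 meets the rule.
- **That both nulls are exceeded six- to seven-fold.** That holds only for moderate/severe events against 0.5%. Against 2% the documents support about 1.8-fold.
- **That safety in HIV-positive men cannot be monitored.** Section 8.1.2 also proposes a sequential boundary for continuous monitoring, section 6.3.1 adds weekly wound follow-up of all HIV-positive men, and the DSMB has already paused and reviewed their surgery.
- **That about 500 HIV-positive men are about to have surgery.** Section 8.4 gives 500 per arm as an enrolment estimate. The number still to be operated on is not stated, and section 10.7.3 shows that some already have been.

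**Conclusion.** The point holds as a set of errors and contradictions within the protocol. Three of four counts are one event too low under the stated exact rule, and the fourth carries a rate of 0.72% where its count gives 0.80%. The denominators of 1,250 and 2,500 conflict with the expected 1,500 and 3,000. At the reported 3.2% and 3.6%, the 0.5% boundary is crossed with near certainty and cannot separate an accepted rate from a worse one. Sections 8.1 and 8.1.2 name different safety populations, and HIV-positive men, the subject of primary objective 2, have no numerical threshold, although other monitoring covers them.

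The count results rest on reading the rule as an exact one-sided 95% binomial bound without adjustment for repeated looks, as the section states. The crossing probabilities assume that the moderate and severe complications of section 10.7.3 are the same class as the moderate/serious events of section 8.1.2, and that each surgery counts at most once.

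**What to change.** In section 8.1.2:
- Decide the denominators and restate the thresholds to match: 34 and 12 at 1,250 with 63 and 20 (0.80%) at 2,500, or 40 and 13 at 1,500 with 74 and 23 at 3,000.
- Name the population of the thresholds and bring section 8.1 into line with it.
- State that the observed moderate/severe rates already exceed the 0.5% boundary.

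In sections 8.1.1, 8.9 and 10.7.3, reconcile the expected and observed rates, and say which severities the 3.6% in section 8.1.1 covers.

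For primary objective 2, report the HIV-positive minus HIV-negative difference in moderate/severe event rates with its confidence interval, from data already collected. Whether the remaining HIV-positive surgeries need a threshold of their own, and with what comparison rate and n, is for the DSMB to set. The documents do not give the number remaining, and taking the trial's own 3.6% as a new null would be a debatable choice made after the fact.

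The cost is one recalculated table and a few sentences. No new data are needed.
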